#### Blinding

An RA from the manager group in The City of Odense performing the allocation of clusters has no contact with the community aged care groups and will be blinded from all aspects of allocation and subsequent intervention. Participants, Care Managers/RD’s, the principal investigator ([name]) and RA’s ([name]) will not be blinded for the intervention. Data will be analyzed by an external RA, who will be blinded for the results of randomization.

#### Analysis

Although this is a pilot study, we do want to explore whether or not there is a difference between groups. All statistical analysis will be performed using a statistics program (SPSS) for Windows. Data will be entered in EXCEL and will subsequently be exported into SPSS software for analysis. All participants will be included in the analysis, regardless of whether they have completed the study or not. Depending on the data type and distribution t-test, Mann-Whitney U test and Chi2 test will be used to compare changes within and between the groups. The model of data analysis needs to consider the effect of clustering; thus, this study will be using effect models with the cluster treaded as a random effect.

The intracluster correlation coefficient (ICC) for quality of life will be calculated by means of ANOVA and published to assess the appropriateness of the sample size assessment in the study.

To assess the feasibility of the outcome measurements the confidence intervals (95% CI) will be calculated to interval estimate the population.

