Three systematic reviews have looked at benefits achieved by means of meals-on-wheels offered to older adults [13–15]. Home-delivered meal programs improve diet quality and increase nutrient intakes among participants [13]. However, more research is needed to evaluate the efficacy and effectiveness of home-delivered meals for older adults on multiple outcomes [14]. Very few randomized controlled studies have assessed the beneficial effect of meals-on-wheels as a supportive intervention [15]. In addition, no randomized controlled intervention studies have been investigating rehabilitation related to limitations of “Activities of daily living” (ADL) e.g. cooking, has any beneficial effect [16].

Support at home such as meals-on-wheels means becoming accustomed to a new mealtime experience. E.g. when still able to cook older adults often hold some control over the foods that are prepared and which they eat, and which helps to foster identity. Foods prepared at home are familiar to the person, holding memories of the past and as well, the activities of grocery shopping, meal planning, and food preparation may help to preserve social, cognitive, and functional abilities.

In this pilot trial, the primary research aim is to explore the community-dwelling older adults acceptability and feasibility of the outcome measurements as methods to measure efficacy of the intervention, and to provide data to estimate the required sample size for a future cluster randomized study of community-dwelling older adults being involved in their own meals in a rehabilitation program.

The second aim of this study is to perform a pilot cluster randomized trial to understand, on an individual level, whether community-dwelling older adults receiving meals-on-wheels experience an improvement in health-related quality of life and muscle strength, being involved in their own meals in a rehabilitation program compared to usual community aged care including receiving meals-on-wheels.

The cluster design is chosen primarily to avoid contamination, since the assigned Health Care Staff and Registered Dieticians receiving additional training could not be expected to treat individual residents differently; respectively the intervention and the control group, by preference of the older person. Also, the cluster design is chosen due to practical reasons, in order not to conflict with other nutritional projects and initiatives in the participating municipality.

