### Sample size

As this is a pilot trial the primary outcome is understanding the feasibility of implementing a large-scale trial. However, to determine sample size for sufficient power to evaluate developmental trajectories of our secondary outcome variables population estimates were derived using data from Beck et al. [42] who had the same design, population and outcome (quality of life by means of EQ-5D-3 L) as in the present study and showed a significant difference between intervention and control group in the EQ-5D-3 L follow-up score of (0.758 [0.222] versus 0.534 [0.355], (*P* = 0.001). Here it was found that the variation seen in quality of life was due to residual variation (the variation from individual to individual) and was not dependent on the clusters. Hence, with a statistical significance level of 0.05 and a power of 80% app. 53 is needed in each group. Estimating a drop-out rate of 20%, due to a longer intervention period than the former study [42], app. 130 participants are needed. This number could probably be included in approximately 10 weeks, for respectively control and intervention group.

The sample size for this trial will be compared with the actually collected samples as to estimate the required sample size for a future cluster randomized trial.

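### Tests of change within each arm do not answer the comparison with usual care; the EQ-5D-3L analysis should be one baseline-adjusted between-arm contrast, with within-arm changes descriptive

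*Protocol article*

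**What the plan says.** All places are in the protocol article.

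- **Aim (Background).** The second aim asks whether participants improve in health-related quality of life and muscle strength "compared to usual community aged care including receiving meals-on-wheels".
- **Size (Sample size).** The effect comes from an earlier study that "showed a significant difference between intervention and control group in the" "EQ-5D-3 L follow-up score of (0.758 [0.222] versus 0.534 [0.355" (read here as mean [SD]). From this, "with a statistical significance level of 0.05 and a power of 80% app. 53 is needed in each group".
- **Tests (Analysis).** After an opening that gives a between-group difference as the interest, the section says that "t-test, Mann-Whitney U test and Chi2 test will be used to compare changes within and between the groups". It then adds a model with the cluster as a random effect, without naming the response variable.
- **Pre-post use (Trial design; Outcomes and Table 1).** A pre- and post-intervention comparison is planned to look at the two parts of the intervention separately. The t=1 assessment that it would use is made in the intervention cluster only. EQ-5D-3L is recorded at t=0, t=1 and t=2.

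**The concern.** The Analysis section commits to significance tests of change inside each arm and lists them beside the between-arm tests without ranking them. A within-arm test asks whether an arm changed. It does not ask whether the arm changed more than usual care did. Regression to the mean, or a time trend shared by both arms, produces within-arm change without any programme effect. A significant change in one arm and a non-significant change in the other is not evidence of a difference between arms. The t=1 comparison has no concurrent control at all.

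Separately, the measure differs between sections: follow-up score for the size, change for the tests, unnamed for the model. Follow-up and change contrasts differ by any baseline difference between the arms. At stake is a clear reading of the exploratory clinical result.

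**Working it through.** **1. The plan's own figure.** Inputs from the Sample size section: difference 0.758 − 0.534 = 0.224; SDs 0.222 and 0.355; alpha 0.05 (two-sided assumed, since the sidedness is not given); power 80%; no cluster inflation, because the variation in the earlier study "was not dependent on the clusters".

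n per arm = 2(1.96 + 0.8416)² SD² / 0.224²

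- Pooled SD = √[(0.222² + 0.355²)/2] = 0.296: 15.70 × 0.0877 / 0.0502 = 27.4, so 28.
- Larger SD, 0.355: 15.70 × 0.1260 / 0.0502 = 39.4, so 40.

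The stated 53 is not reproduced at 80% power. It does appear with SD 0.355 and 90% power. The total follows from 53: 106/0.8 = 132.5, so 133, or 106 × 1.2 = 127.2, so 128, against about 130 stated. So 53 cannot be relabelled as the size for another contrast without a new calculation.

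**2. Within-arm tests when both arms change equally.** Assumptions: 53 evaluable per arm, independent participants, paired t-test at two-sided 0.05, same true change in both arms. The documents give neither the common change nor the SD of change, so a range is shown in units of the SD of change. With p the power of the paired test (noncentral t), the chance that the intervention arm is significant and the control arm is not is p(1 − p).

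| Common change (SD of change) | p | Intervention arm only |
|---|---|---|
| 0 (improvement only) | 0.025 | 0.025 × 0.95 = 2.4% |
| 0.1 | 0.110 | 9.8% (9.5% counting improvement only) |
| 0.2 | 0.298 | 20.9% |
| 0.27 | 0.488 | 25.0% |
| 0.4 | 0.815 | 15.1% |

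The value 25% is the maximum of p(1 − p). It is reached at any sample size for some common change, so it is a ceiling and not an expected rate.

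A simulation on the EQ-5D-3L scale agrees (20,000 runs, SD 0.296, assumed correlation 0.5, so SD of change 0.296). Common changes of 0.03, 0.05, 0.08, 0.10, 0.15 and 0.224 give 10%, 18%, 25%, 22%, 5% and 0%. The between-arm t-test on change stays at about 5% two-sided throughout, that is 2.5% in favour of the programme.

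**3. Change against baseline-adjusted follow-up.** With equal variance σ² at t=0 and t=2, correlation r, and clustering ignored:

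- change score: 2σ²(1 − r)
- baseline-adjusted follow-up: σ²(1 − r²)
- ratio of adjusted to change: (1 − r²)/[2(1 − r)] = (1 + r)/2

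The documents give no r. For an assumed 0.3, 0.5 and 0.7 the ratio is 0.65, 0.75 and 0.85. Unadjusted follow-up has variance σ², so a change comparison is no worse than follow-up once r is 0.5 or more.

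**The case against.** The strongest reply is that the direction of the comparison is already fixed. The second aim and the opening of the Analysis section both point to intervention against usual care. The primary outcome is data completion and assessment of sample size, so no clinical contrast decides this trial. That stands, and it limits the point. The Secondary outcomes section does call quality of life the primary outcome, but that is a separate labelling conflict.

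A reader might infer three stronger things. None is supported.

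- **That a within-arm p-value would be presented as a programme effect.** The protocol does not say so. It only leaves such tests in place without a stated role beyond the pre-post comparison of the two intervention parts.
- **That sizing on follow-up score causes the false intervention-only signal.** It does not. The signal comes from within-arm testing alone, and the difference between follow-up and change is a second, milder inconsistency.
- **That a false signal occurs a quarter of the time.** That holds only near one assumed common change. The rate is about 2% at none and close to 0 at a large one.

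It can also be said that the choice of response and covariates belongs in an analysis plan. That would answer a complaint about missing detail. Here the article positively commits to tests of change within groups, which is a stated choice with a better alternative. Finally, the variance ratio shows that a change comparison is less efficient, not that it is invalid. A baseline difference between three and two areas is possible, but the documents do not show that it is likely.

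**Conclusion.** The point holds in a limited form. The planned within-arm significance tests do not address the second aim. With no programme effect they can show improvement in the intervention arm only, with probability from about 2% to at most 25%, falling back towards 0 for large common changes. This assumes 53 per arm, independent participants, paired t-tests and equal true change. The change comparison between arms is valid under equal change but less precise than a baseline-adjusted one, by the factor 0.65 to 0.85 for an assumed r of 0.3 to 0.7. The size, meanwhile, rests on an unadjusted follow-up score. All these figures ignore clustering. Because the outcome is exploratory and the between-group interest is stated, this is a worthwhile improvement and not a fault that undermines the pilot.

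**What to change.** **Analysis section.** Replace the sentence on tests of change. Make the exploratory EQ-5D-3L comparison the between-arm difference at t=2, adjusted for the participant's t=0 score, within the random-effect model for area already planned. Use the same form for chair stand and the other continuous outcomes with baseline values.

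**Within-arm results.** Report changes within each arm descriptively, as means with 95% confidence intervals, without significance tests, and state that no effect is claimed from them. Apply this also to the intervention-only comparisons across t=0, t=1 and t=2 that the Trial design and Outcomes sections foresee.

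**Sample size section.** Say only that the size was based on the unadjusted between-arm follow-up score. Do not describe it as powered for the adjusted contrast unless it is recalculated. The quoted inputs give 28 to 40 per arm at 80% power even for the unadjusted contrast, not 53.

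**Cost.** Wording only. EQ-5D-3L is already collected at t=0 and t=2. What is given up is the within-arm p-values.

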### Trial design

This study is a cluster randomized trial where clusters are a total of five community aged care areas in The City of Odense allocated into groups of two clusters. The two clusters are 1) the group of older adults being involved in own meals in a rehabilitation program (Intervention) (*n* = 3) and 2) usual care (Control) (*n* = 2). In the City of Odense there are 33,800 citizens above 65 years of age, and totally residents receiving support at home are 5453 (18+ years of age). 1477 citizens (18+ years of age) are receiving meals-on-wheels.

The intervention in the study consists of two parts (see below) targeted at individual participant level, and to separately investigate the two parts of the intervention a pre- and post-intervention comparison will be made.

An overview of the trial is presented in Fig. 1 Design of the study and flow of participant.

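### The Analysis section names participant-level tests beside a random-effect model without saying which governs, leaves the level of *cluster* open, and names unpaired tests for within-group change

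*Protocol article*

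**What the plan says.** Three statements in the Analysis section of the Protocol article bear on this:

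- On tests: "t-test, Mann-Whitney U test and Chi2 test will be used to compare changes within and between the groups", with the choice depending on data type and distribution.
- On clustering, in the next sentence: "this study will be using effect models with the cluster treaded as a random effect".
- On the analysis set: "All participants will be included in the analysis, regardless of whether they have completed the study or not".

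The same section plans an ICC for quality of life by ANOVA, to judge whether the sample size was appropriate. Trial design adds a pre-post comparison to look separately at the two parts of the intervention.

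The word *cluster* has two meanings:

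- **The arm:** the Abstract (Methods) and Participants sections speak of an intervention cluster made up of three areas and a control cluster made up of two.
- **The area:** Sequence generation and Allocation concealment mechanism call the community aged care areas the clusters.
- **Both:** Trial design first says that the clusters are the five areas, then that these are "allocated into groups of two clusters".

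The Sample size section sets 53 per group and, with 20% drop-out, "app. 130 participants are needed".

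**The concern.** Two between-arm analyses are specified, and they can give different answers. A t-test, Mann-Whitney or Chi2 test on individual participants assumes independence, while a random-effect model allows for correlation within areas. With no precedence stated, the choice of p-value is open after the data are seen. The Sample size section reports that earlier variation did not depend on clusters, which makes it easier to fall back on the unadjusted tests.

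The unsettled meaning of *cluster* reaches one of the pilot's main aims. The ICC is meant to inform the size of a future cluster trial. Calculated across areas within arm, it measures what that trial needs. Calculated across the two arms, it measures the treatment difference.

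For within-group change the data are two measurements on the same person. Mann-Whitney and Chi2 compare separate groups of people, and no paired counterpart is named. Finally, a participant without a follow-up value has no change score, so tests on change sit badly with the statement that everyone is analysed.

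**Working it through.** **Inputs.** From the protocol: 53 per group, 20% drop-out, about 130 in total, 3 against 2 areas, planning values "0.758 [0.222] versus 0.534 [0.355". Assumed: equal split of participants over the areas within each arm (18, 18, 17 against 27, 26), the ICC of the analysed variable, and the baseline/follow-up correlation r.

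**The plan's own figure.** With n = 2(1.96 + 0.842)² SD²/0.224², the stated 80% power gives 28 per group (SD 0.296, root mean square of the two) or 40 (SD 0.355), not 53. Of the variants tried, only 90% power with SD 0.355 gives 53. That is a separate matter. Here 53 serves only as the number analysed per arm, and the drop-out step agrees with it: 106/0.8 = 133 and 106 × 1.2 = 128, against about 130.

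**1. Unadjusted between-arm t-test.** With total variance 1, the true variance of the difference in means is

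V = ICC × [(18² + 18² + 17²)/53² + (27² + 26²)/53²] + (1 − ICC) × 2/53 = ICC × 0.834 + (1 − ICC) × 0.0377.

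The t-test uses roughly 0.0377, so its true type I error is about 2[1 − Φ(1.96/√(V/0.0377))].

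| ICC (assumed) | V/0.0377 | Formula | Simulation, 40,000 runs | t-test on five area means, 3 df |
|---|---|---|---|---|
| 0 | 1.00 | 5.0% | 5.1% | 4.4% |
| 0.01 | 1.21 | 7.5% | 7.5% | 4.6% |
| 0.02 | 1.42 | 10.0% | 10.1% | 4.6% |
| 0.05 | 2.05 | 17.2% | 17.5% | 4.8% |
| 0.10 | 3.11 | 26.6% | 27.3% | 4.8% |

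**2. Level of the random effect.** At arm level there are two units and two arm means, which leaves 2 − 2 = 0 degrees of freedom. In trial fits the standard error of the arm effect was about 1.4 outcome SDs and no fit rejected. At area level 5 − 2 = 3 degrees of freedom remain, so treatment and cluster can be separated. Ordinary Wald tests are still too liberal there: rejection was 5.3% at ICC 0 and 11.2% at ICC 0.05 (300 fits per setting, 81% and 95% usable).

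**3. Level of the ICC.** Take the planning values, 53 per arm and no area variation at all.

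- Between-arm mean square: 53 × 0.224²/2 = 1.330.
- Within-arm mean square: (0.222² + 0.355²)/2 = 0.0877.
- Arm-level ANOVA ICC: (1.330 − 0.0877)/(1.330 + 52 × 0.0877) = 0.21.

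That value is produced entirely by the treatment difference.

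**4. Pairing.** Take n = 53, a change of 0.3 SD and r = 0.6.

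- True standard error: √(2 × 0.4/53) = 0.123. Standard error used by an unpaired test: √(2/53) = 0.194, a ratio of 1.58.
- Paired power: Φ(0.3/0.123 − 1.96) = 68%.
- Unpaired power: rejection needs a difference of 1.96 × 0.194 = 0.381, so power is Φ((0.3 − 0.381)/0.123) = 26%.
- Unpaired true alpha: 2[1 − Φ(1.96 × 1.58)] = 0.2%.

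Simulation (100,000 runs) gave 67%, 25% and 0.2%. Over r = 0.3, 0.5 and 0.7, the formula gives paired power of 45%, 59% and 80%, unpaired power of 31%, 28% and 22%, and unpaired alpha of 1.9%, 0.6% and 0.03%.

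**5. Non-completers.** 130 × 0.20 = 26 participants would have no change score.

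**The case against.** The strongest reply is that the section read as a whole is sound in intent. It states that clustering must be considered, it names a random-effect model and it plans an ICC. The sections on allocation make the area the unit. Missing-data detail may sit in an analysis plan that is not shown, the wording is condensed, and the trial is a pilot.

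Much of this stands, and it rules out four stronger readings that a reader might infer:

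- *The plan ignores clustering.* It does not. The sentence after the tests addresses it. The fault is that both analyses are stated and neither is given precedence.
- *Cluster is defined as the arm, so the model cannot separate cluster from treatment.* The documents also define the five areas as clusters, and at that level 3 degrees of freedom remain. The confounding holds only on the arm reading.
- *All the named tests are wrong for within-group change.* The word t-test may mean the paired test. The point is firm only for Mann-Whitney and Chi2, which are also legitimate in form for comparing changes between independent groups.
- *Non-completers cannot be included.* A repeated-measures model or imputation could include them. The conflict is with the tests on change.

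What the reply does not remove is the conflict within one section, or the fact that the text on the random effect and the ICC does not say which of the two meanings of *cluster* applies. These are things the article states, not details left to another document.

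**Conclusion.** The point holds as an unresolved specification with measurable consequences, and it should be fixed. Reporting the unadjusted t-test would raise the between-arm type I error from 5% to about 7.5%, 10% or 17 to 18% at ICCs of 0.01, 0.02 or 0.05. At an ICC of exactly 0 there is no inflation. An unpaired test on within-group change errs the other way, with power of about 25% instead of 68% at r = 0.6. These sizes rest on assumed ICCs, an assumed r and an equal split over areas, and they apply only if those tests are the ones reported. The ambiguity over the level of the random effect and the ICC needs no assumption, because it is in the text.

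The completion ratios, which are the primary feasibility outcome, are unaffected, and the group comparison is described as exploratory. That keeps the point below the level of a fault that must be corrected before the trial can be interpreted. The ICC is what lifts it above mere wording, because an arm-level value would be useless for sizing the future trial.

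**What to change.** 1. **Remove the participant-level between-group tests** and let one area-aware analysis govern. Two forms are suitable: a mixed model of follow-up adjusted for baseline, or a repeated-measures model of t = 0 and t = 2 with a within-participant covariance or participant random effect. In the second form baseline is an outcome and must not also be a covariate.
2. **Put a random intercept on area (five levels), never on arm.** In the repeated-measures form add an area-by-time term, because a constant area effect cancels from a contrast of changes. Use small-sample inference, or a test on area-level summaries with 3 df.
3. **State that the ICC is calculated across areas within arm**, and report its interval. With 3 df it will be imprecise.
4. **For within-group change** name the paired t-test, Wilcoxon signed-rank, and McNemar or marginal homogeneity.
5. **State how missing follow-up is handled.** The repeated-measures form keeps participants who have only a baseline value. The baseline-adjusted form needs imputation or a narrower statement of who is analysed.
6. **Use *area* for the five units and *arm* for the two groups throughout.**

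The cost is wording, a little programming and wider between-arm intervals. For a difference of 0.224 with 53 per arm, the 3-df test has power of 73%, 66% and 46% at ICCs of 0, 0.01 and 0.05 with SD 0.296, and 59%, 52% and 35% with SD 0.355. That is what five areas can support.

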**Methods:**

This cluster randomized controlled study will consist of two clusters of a total of 5 community aged care areas; the intervention cluster, which hold 3 community aged care areas and the control cluster which hold 2 areas. The 130 community-dwelling older adults, receiving meals-on-wheels, will randomly be allocated to either the intervention cluster consisting of 8 weeks of participation in a rehabilitation program led by a Case Manager or the control cluster receiving usual community aged care. The primary outcome will be assessment of data collection (ratio between completed- and non-completed data) and assessment of sample size. The secondary clinical outcomes will be health-related quality of life (EQ-5D-3 L), muscle strength (chair stand), nutritional status (weight/BMI), loneliness (UCLA scale), mental well-being (Warwich-Edinburgh scale), self-efficacy (General Self-Efficacy scale), satisfaction with food-related life (SWFL scale) and refrigerator content.

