In the present study, goals will be short-term (i.e. realistic to reach within the intervention period), and a maximum of three goals will be selected for change.

Thus, the Case Managers will encourage participants to involve in these activities.

When *implementing* the activities in relation to meals the Care Manager/RD will plan the intervention interdisciplinary with other professionals within The City of Odense e.g. Occupational Therapist, Physiotherapist, Health Care and Kitchen Staff. A period of eight weeks is chosen for the rehabilitation program in order to get a realistic comparison. This is the minimum amount of time for a Danish municipality rehabilitation program [21]. The intervention is individual and will consist of a minimum of three contacts to the Case Manager/RD in order to *monitor* and *reassess*. After completion of the rehabilitations program a final evaluation will be made.

The participants in the control group will receive usual care in relation to meals; this includes a number (one to seven) hot meals-on-wheels arriving one to three times per week, along with usual support at home.

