### Outcomes

The outcome assessments, conducted in the participants homes by Research Assistants (RA) and Case Managers/RD’s will occur at inclusion (Baseline, *t* = 0) and at the end of the intervention period (Follow-up, *t* = 2). At the beginning of second part of the intervention some outcome assessments will also be conducted in only the Intervention cluster (In between, *t* = 1). It is, however, not obtained by the same person at baseline, in between, and follow-up for practical reasons. However, all will receive the same training in the methods on obtaining outcome assessments by RA ([name]) or RA ([name]). Due to the design of the study it is not possible to blind neither the RA’s nor the Case Managers/RD’s. An overview of the outcome measurements is presented in Table 1 and described in detail below.

**Table 1 Tab1:** Data collection 2 Content in fridge (sufficient, insufficient, empty)

Measure	Time of data collection		
	Baseline *T* = 0	In between *T* = 1	Follow-up *T* = 2
Quality of life by EQ-5D-3 L	X	X	X
Height, meter	X	X	X
Weight, kg	X	X	X
BMI, (kg*kg/m2)	X	X	X
Muscle strength - Chair stand^1^	X	X	X
Satisfaction with food-related life	X	X	X
UCLA Loneliness Scale	X		X
The Short Warwich-Edinburgh Mental Well-being Scale	X		X
General Self Efficacy Scale	X		X
Refrigerator content^2^	X		X
Sociodemographic	X		
Meals-on-wheels (days/w)	X		

^1^Rise from a chair without using the arms in 30 s

^2^Content in fridge (sufficient, insufficient, empty)

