The satisfaction with food-related life will be measured by the Satisfaction with Food-related Life (SWFL) scale (at *t* = 0, *t* = 1, *t* = 2). The SWFL, consists of 5 items grouped into a single dimension (e.g. Food 1: Food and meals are positive elements; Food 2: I am generally pleased with my food; Food 3: My life in relation to food and meals is close to ideal; Food 4: With regards to food, the conditions of my life are excellent; Food 5: Food and meals give me satisfaction in daily life.). In each scale, the respondents must indicate their degree of agreement with these statements using a 5-level Likert scale (1 = disagree completely, 5 = agree completely). Each item will be calculated and reported separately and totally [39].

A picture of the participants’ refrigerator will be used to assess the qualitative and quantitative contents of refrigerators (at *t* = 0, *t* = 2). The categories will be “sufficient”, “in-sufficient” (e.g. with old food, according to date or appearance) or “empty” (less than 3 solid food) [40, 41].

For each participant sociodemographic data will be collected; this include age, marital status and yes/no if living alone (at t = 0). Also, data describing numbers of meals delivered by meals-on-wheels on a weekly basis will be collected.

Compliance i.e. use of and participation in possible and suggested activities in relation to meals, number of visits from Dieticians and other staffs involved, plus reasons for canceling of such planned visits and unintended adverse events/possible problems related to the suggested intervention strategies will be recorded during the 8 weeks of intervention period.

After each contact (visit or telephone) with participant following information will be registered by the Case Manager/RD:who were present at the meeting if the contact was a visit,which interdisciplinary contact within the municipality was made afterwards,the time spent on the specific contact,the Case Managers/RD’s judgment (yes/no) if the participants were motivated in the collaboration, andany unintended adverse events/possible problems related to the suggested intervention.

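### The between-arm tests use raw changes without covariates, and the random-area model names none, although the baseline scores and covariates for an adjusted model are collected

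*Protocol article*

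**What the plan says.** The Analysis section of the protocol article gives two elements for the comparison of arms. The first is a set of tests: depending on data type and distribution, "t-test, Mann-Whitney U test and Chi2 test will be used to compare changes within and between the groups". The second follows from clustering: "this study will be using effect models with the cluster treaded as a random effect". No fixed covariate is named for either.

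Several candidate covariates are collected. Table 1 has every outcome scale measured at both t=0 and t=2. Under Secondary outcomes, "For each participant sociodemographic data will be collected; this include age, marital status and yes/no if living alone", and "data describing numbers of meals delivered by meals-on-wheels on a weekly basis will be collected"; Table 1 places the latter at baseline. In usual care the meal count varies widely: "this includes a number (one to seven) hot meals-on-wheels arriving one to three times per week".

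The Abstract describes the allocation as "the intervention cluster, which hold 3 community aged care areas and the control cluster which hold 2 areas". Participants says the five areas are assigned at random. Sequence generation says the choice took account of which areas were next in line for staff education. Implementation has the intervention areas recruited first and the control areas afterwards.

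**The concern.** A t-test, a Mann-Whitney U test or a chi-squared test takes no covariate. A random area effect widens the standard error to allow for area-to-area variation, but it does not remove a systematic difference between three areas and two. If the arms start at different EQ-5D levels, a comparison of raw changes mixes the intervention effect with regression to the mean. If they differ in age, household or meal frequency, any effect of those variables on the change is mixed in as well.

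The comparison matters beyond description. The second aim is to learn whether quality of life and muscle strength improve against usual care, and the Conclusions say the results will be used to design a definitive trial. A distorted or needlessly imprecise contrast would carry forward.

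**Working it through.** The plan gives no figure on this point: no baseline to follow-up correlation, no baseline difference and no non-zero ICC. Those values are assumed below and shown over a range.

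**Inputs from Sample size.** EQ-5D-3L at follow-up is 0.758 [0.222] against 0.534 [0.355], with the brackets read as SDs.
- Difference: 0.758 - 0.534 = 0.224.
- Pooled SD: sqrt((0.222² + 0.355²)/2) = 0.296.

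**Step 1: what the change comparison leaves in.** Let D be the baseline difference (intervention minus control). Assume equal SDs at both times, and that without an intervention effect both arms follow the same regression of follow-up on baseline, with slope r. The expected follow-up difference is then rD, and the expected difference in change is rD - D = -(1-r)D. Adjustment for the baseline score leaves about zero under the same assumption.

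With an assumed D of 0.25 SD = 0.25 × 0.296 = 0.074:

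| r (assumed) | -(1-r) × 0.074 | share of 0.224 |
|---|---|---|
| 0.3 | -0.052 | 23% |
| 0.5 | -0.037 | 17% |
| 0.7 | -0.022 | 10% |
| 0.8 | -0.015 | 7% |

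If the intervention arm starts higher, the change comparison understates the effect. If it starts lower, it overstates it. The result scales with D: D = 0.05 gives -0.035, -0.025, -0.015 and -0.010.

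**Step 2: precision.** Relative to a follow-up-only comparison, the individual-level variance is 2(1-r) for change and 1-r² with the baseline as covariate. Their ratio is (1+r)/2, so adjustment saves (1-r)/2.

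| r (assumed) | change, 2(1-r) | adjusted, 1-r² | reduction |
|---|---|---|---|
| 0.3 | 1.40 | 0.91 | 35% |
| 0.5 | 1.00 | 0.75 | 25% |
| 0.7 | 0.60 | 0.51 | 15% |
| 0.8 | 0.40 | 0.36 | 10% |

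**Step 3: is 0.25 SD a reasonable imbalance to consider?** Suppose the areas had been drawn by chance, with 65 people per arm spread evenly over the arm's areas. The SD of a standardised baseline difference is sqrt(ICC × (1/3 + 1/2) + (1-ICC) × 2/65). At assumed ICCs of 0, 0.02 and 0.05 this is 0.175, 0.216 and 0.266, and the probability of exceeding 0.25 SD in either direction is 15%, 25% and 35%. These figures show only that such an imbalance would not be unusual. They are not evidence of bias, since chance imbalance is part of sampling error.

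**Step 4: why imbalance here may be more than chance.** Sequence generation ties the choice of areas to an administrative schedule, while Participants calls it random. Recruiting the arms one after the other adds a difference in calendar time.

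**The case against.** The strongest reply is that this is an argument from silence. The sentence on random-effect models neither lists nor excludes fixed effects, and a covariate list commonly stands in a statistical analysis plan or full protocol, neither of which is shown. That is right as far as the model goes: a reader might infer that area is its only extra term, and the text does not say so. It does not cover the tests, which the article does name and which cannot be adjusted.

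A reader might also infer that baseline differences pass straight into the effect estimate. They do not, because the tests compare changes and each person's baseline is already subtracted. Only the residue in step 1 remains. For the same reason, multiplying an imbalance in age or meals by its association with the EQ-5D level would be wrong: that suits a follow-up-only comparison. A covariate equally related to EQ-5D at both times cancels from the change. The documents give no association with change, so no size can be put on that part. Nor do they say who provides the meals that are not delivered, so meal frequency as a marker of own cooking is only a supposition.

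Two further replies stand in part. The precision gain is modest when r is high. And in groups not formed by chance, adjusted and change-score estimates can disagree with neither guaranteed unbiased: if a baseline gap between areas is a stable one, the change score is the better of the two.

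Finally, the trial is a pilot. Its primary outcome, data completion, and the planned ANOVA estimate of the ICC are untouched by covariate adjustment.

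**Conclusion.** The point holds in limited form. The article specifies between-arm tests on raw changes that take no covariates, and a random-area model for which none is named, while the data for a better analysis are being collected. For an assumed baseline EQ-5D difference of 0.074, the residue in the change comparison is about -0.052 to -0.022 for r between 0.3 and 0.7. The variance saving from baseline adjustment is 35% to 10% for r between 0.3 and 0.8.

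The first figure rests on the assumed imbalance, the assumed r, equal SDs and a common regression line in both arms. The second rests on r and equal SDs, and concerns individual-level variance only. Neither is a prediction of what this trial will show. Adjustment improves the contrast but does not make a three-against-two comparison of schedule-chosen areas equivalent to a randomised one.

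**What to change.** For each continuous outcome, make the between-arm analysis a mixed model of the t=2 score on arm, with area as random effect and the baseline score, age, living alone and delivered meals per week as fixed covariates. Report the unadjusted change comparison beside it, so that any disagreement is visible. Present the contrast as exploratory, and say that unmeasured area differences and calendar time remain. Reconcile Participants with Sequence generation on how the areas were assigned, since the interpretation depends on it.

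The cost is a few lines of analysis text. No new data are needed, and covariates that vary between individuals draw mainly on individual-level information, not on the few degrees of freedom between areas.
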